### Recruitment

#### General Practitioners

Strategies to recruit GPs to the project were: telephone calls, followed up with emails and postal mail. To maintain engagement, GPs within the control group will be offered the intervention training and resources after the trial is complete. GP recruitment took place from May to December 2022.

### Patients

Participating GPs began recruiting patients in May 2022 and ended late August 2023. Participants can access the patient-reported outcome questionnaire via e-Boks, a widely used Danish digital platform for secure communication with public authorities and private companies.

Patients lacking access to e-Boks or who were unable to complete the electronic questionnaire, will be provided a hard copy by their GP or schedule a phone interview with a member of the research team.

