### Outcomes

#### Primary outcome

This study primarily investigates longitudinal changes in DD at baseline, 4 months, and 12 months. The DDS is a validated and reliable 17-item self-report tool that measures emotional burden, regimen-related distress, physician-related distress, and interpersonal distress [5, 10, 12]. Participants rate items on a six-point Likert scale, with overall and subscale scores calculated by averaging responses. Physician-related distress might be a key focus in the analysis, as it may be directly influenced by the intervention.

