## Methods: assignment of interventions (for controlled trials)

### Allocation

GPs were randomized into intervention or control clusters at a 1:1 allocation ratio using a computer-generated block size of six. The GPs were stratified into two groups, taking their capacities into account (One with general practitioners with 1 or 2 capacities, and another with 3 or more capacities). This approach aimed to ensure a homogeneous distribution of small and large general practices in each intervention arm. A statistician blinded to the practice identities performed the allocation, and the process was concealed within sealed envelopes. These sealed envelopes where then opened by SDCO in the correct order, when allocating GPs, to minimize the risk of unintentional allocation bias or interference.

The control group in this study is subject to “usual care,” which encompasses the routine practices and treatments typically administered by GPs or a diabetic nurse for patients diagnosed with T2DM.

Usual care, by its nature, is subject to variation as it is contingent upon the individual practices of the GPs, their interpretation of the patient’s needs, and adherence to national guidelines. In Denmark, there are established clinical guidelines for the management and treatment of T2DM, and while we anticipate that several GPs in the control group will adhere to these guidelines, it is important to acknowledge that the extent and nature of adherence may vary.

In the context of these national guidelines, usual care may involve the patient receiving three consultations to gather information about T2DM, understand how to manage the disease, learn about available treatment options, and receive referrals for screenings of potential complications, health-education programs, and lifestyle interventions. However, due to the variance in practices across different healthcare providers, the application of these guidelines may not be uniform.

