### Blinding

The study design does not allow blinding of GP. However, patients are blinded as they enter the study unaware of their treatment, ensuring genuine responses. Data analysts are also kept in the dark, maintaining unbiased data interpretation.

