## Methods: data collection, management, and analysis

### Data collection methods

The present study utilizes an electronic patient-reported questionnaire as the primary method for data collection, with the option of completing a hard copy or telephone version of the questionnaire. The questionnaire was designed to gather information on outcomes that are deemed essential to the study’s objectives. These outcomes were selected based on their validation as reliable tools for measuring key outcomes. To ensure participant confidentiality and data integrity, each participant is assigned a unique, anonymized ID, concealing identities from data analysts.

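### For patients who cannot answer electronically, the unblinded GP hands out the primary-outcome questionnaire, or a team member whose masking is not described conducts it by phone: an avoidable risk of reporting bias of unknown, possibly negligible size

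*Protocol article*

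**What the plan says.** Electronic self-completion is the default. Data collection methods describes an "electronic patient-reported questionnaire as the primary method for data collection, with the option of completing a hard copy or telephone version of the questionnaire". Under Recruitment, Patients, those without e-Boks, or unable to complete the electronic form, "will be provided a hard copy by their GP or schedule a phone interview with a member of the research team".

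Blinding covers three groups:
- GPs: "The study design does not allow blinding of GP".
- Patients: "patients are blinded as they enter the study unaware of their treatment, ensuring genuine responses".
- Analysts: "Data analysts are also kept in the dark, maintaining unbiased data interpretation".

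Interviewers are not mentioned.

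The DDS has four subscales. Of one of them, Primary outcome says: "Physician-related distress might be a key focus in the analysis, as it may be directly influenced by the intervention". Perceived quality of care, measured with study-specific items at the same visits, is a secondary outcome. Under Allocation, the envelopes were held by the centre that developed the intervention: "These sealed envelopes where then opened by SDCO in the correct order, when allocating GPs".

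**The concern.** It is unavoidable that GPs know their arm. It is avoidable that they hand out the outcome form. A patient who receives from their own doctor a questionnaire about that doctor's care may answer more kindly. If this is stronger, or paper is used more often, in one arm, the arm difference moves. The exposure is greatest on the physician-related subscale, which the article singles out, and on the perceived-care items.

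The phone route puts a person between the patient and the answer. Allocation is by practice, so anyone who knows a patient's practice and that practice's allocation knows the arm.

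The Discussion treats unblinded GPs as a risk to intervention delivery and patient selection, but not to outcome collection. The assurance of genuine responses in Blinding rests on what patients know. It does not address who hands over or reads out the form.

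**Working it through.** The article gives no figure on this point, so there is none to reproduce. The check has two parts.

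**1. The passages side by side**

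| Route | Who stands between patient and answer | Masking stated in the article |
|---|---|---|
| Electronic (default) | nobody | not applicable |
| Paper | the GP provides the form; return route not described | GP not blinded |
| Phone | a research team member | not stated |

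For paper, the exposure follows from what the article states: an unblinded GP, who is also the subject of some items, provides the form. For phone, the article is silent on masking.

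**2. Possible size (illustration only)**

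Let p be the share of patients answering by the fallback routes and b the mean shift in their DDS score due to the route, with I and C for the intervention and control arms. The shift in the arm difference is

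p_I × b_I − p_C × b_C.

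- If shares are equal, this is p × (b_I − b_C). Courtesy of equal strength in both arms cancels.
- If the effect is equal but the shares differ, it is (p_I − p_C) × b. For example, with shares of 20% and 10% and b = 0.5, it is 0.10 × 0.5 = 0.05 points.

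The table gives p × (b_I − b_C) for equal shares. Both inputs are assumed, since the article gives neither.

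| Share p | Difference 0.1 | Difference 0.25 | Difference 0.5 |
|---|---|---|---|
| 5% | 0.005 | 0.013 | 0.025 |
| 10% | 0.010 | 0.025 | 0.050 |
| 20% | 0.020 | 0.050 | 0.100 |
| 30% | 0.030 | 0.075 | 0.150 |

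The range is thus 0.005 to 0.15 points on a 1 to 6 scale, and 0 if the effect does not differ between arms.

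For scale, take the planned 16 clusters of 6 per arm and an intraclass correlation of 0.05. The design effect is 1 + 5 × 0.05 = 1.25, and the effective size is 96 / 1.25 = 76.8 per arm. The detectable difference at 80% power is (1.960 + 0.842) × √(2 / 76.8) = 0.45 standard deviations. The article gives no standard deviation, so this cannot be set against the range in DDS points.

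One factor reduces the shift further. The outcome is followed from baseline, so a route effect that stays constant within a patient largely cancels in the change from baseline.

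**The case against.** Much of the case on the other side stands.

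- **Collected by people who know the arm.** A reader might infer this of the primary outcome as a whole. The article does not support it. Electronic completion is the default, the GP is said only to provide the paper form, the patient still fills it in, and nothing says that the GP collects or sees the answers.
- **Interviewers who know the arm.** A reader might also infer this because "These sealed envelopes where then opened by SDCO in the correct order". The article does not say that those staff make the calls. Interviewer masking, scripts and paper returns are details that an article commonly leaves to the full protocol, which is not shown. The phone route is therefore a point to clarify, not a demonstrated fault.
- **Only analysts masked.** This would misread Blinding, which also claims masking of patients at entry, and patients are the raters.
- **Direction of bias.** The GP hands out paper in both arms, so courtesy towards one's doctor is not in itself a bias between arms. Intervention GPs receive individual meetings and materials during the trial, while control GPs are offered them afterwards. That makes a difference plausible, but nothing in the article shows one or fixes its direction.
- **Purpose of the fallback.** It retains patients who might otherwise be lost in a trial expecting 40% dropout, so removing it would do harm.

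The objection does not remove the paper route. The choice of the GP as the person who provides the form is stated in the article, is not needed for the design, and concerns an instrument that partly rates that GP.

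**Conclusion.** The point holds in a limited form. For patients who cannot answer electronically, the stated paper route exposes a self-rated primary outcome to an unmasked party whose care it partly rates. The masking of the alternative phone route is not described.

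The size is unknown. The range of 0.005 to 0.15 DDS points rests wholly on an assumed share of 5% to 30% and an assumed difference between arms of 0.1 to 0.5 points. A difference of zero is also consistent with the article. A reader should not take the range as an estimate of bias, nor conclude that the result will favour the intervention.

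The change is worth making because it is cheap. The risk does not invalidate the primary comparison.

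**What to change.** For follow-up questionnaires still outstanding, amend Recruitment, Patients:

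1. Post paper forms from the data unit (OPEN) to the patient's home, with prepaid return to that unit, so that they do not pass through the practice.
2. Have phone interviews done from a fixed script by existing staff who do not see the allocation, and say so under Blinding.
3. Record completion mode (electronic, paper, phone) at each visit and report it by arm.
4. Treat any analysis by mode, or in electronic responders only, as supportive. Mode may be affected by allocation, so restricting to one mode conditions on a possibly post-randomisation variable.

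**What can still be reached.** Recruitment ended in late August 2023, so baseline forms cannot be changed. At the version date of 24 October 2023, and counting from enrolment, 4-month forms were outstanding for patients enrolled after about 24 June 2023, and 12-month forms for those enrolled after about 24 October 2022. By publication on 21 March 2024, only 12-month forms for patients enrolled after about 21 March 2023 remained, the last due around the end of August 2024. Once collection has ended, only steps 3 and 4 apply, and only if mode was recorded.

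**Cost.** Postage, some reassignment of calls and one table. Paper returns may fall slightly. Fallback patients would also change route between early and later visits, so a route effect at baseline would no longer cancel in the change from baseline for them. Recording mode at each visit lets this be described.

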### Participant timeline

The time schedule for the enrolment of both GPs and patients is presented in Fig. 1.

**Fig. 1 Fig1:**
[figure not shown]
Time schedule of enrolment

## Methods: assignment of interventions (for controlled trials)

### Allocation

GPs were randomized into intervention or control clusters at a 1:1 allocation ratio using a computer-generated block size of six. The GPs were stratified into two groups, taking their capacities into account (One with general practitioners with 1 or 2 capacities, and another with 3 or more capacities). This approach aimed to ensure a homogeneous distribution of small and large general practices in each intervention arm. A statistician blinded to the practice identities performed the allocation, and the process was concealed within sealed envelopes. These sealed envelopes where then opened by SDCO in the correct order, when allocating GPs, to minimize the risk of unintentional allocation bias or interference.

The control group in this study is subject to “usual care,” which encompasses the routine practices and treatments typically administered by GPs or a diabetic nurse for patients diagnosed with T2DM.

Usual care, by its nature, is subject to variation as it is contingent upon the individual practices of the GPs, their interpretation of the patient’s needs, and adherence to national guidelines. In Denmark, there are established clinical guidelines for the management and treatment of T2DM, and while we anticipate that several GPs in the control group will adhere to these guidelines, it is important to acknowledge that the extent and nature of adherence may vary.

In the context of these national guidelines, usual care may involve the patient receiving three consultations to gather information about T2DM, understand how to manage the disease, learn about available treatment options, and receive referrals for screenings of potential complications, health-education programs, and lifestyle interventions. However, due to the variance in practices across different healthcare providers, the application of these guidelines may not be uniform.

### Blinding

The study design does not allow blinding of GP. However, patients are blinded as they enter the study unaware of their treatment, ensuring genuine responses. Data analysts are also kept in the dark, maintaining unbiased data interpretation.

## Methods: data collection, management, and analysis

### Data collection methods

The present study utilizes an electronic patient-reported questionnaire as the primary method for data collection, with the option of completing a hard copy or telephone version of the questionnaire. The questionnaire was designed to gather information on outcomes that are deemed essential to the study’s objectives. These outcomes were selected based on their validation as reliable tools for measuring key outcomes. To ensure participant confidentiality and data integrity, each participant is assigned a unique, anonymized ID, concealing identities from data analysts.

### Data management

The present study utilizes e-Boks and the Open Patient data Explorative Network (OPEN) for the collection of data. The survey instrument has been developed using OPEN REDCap, and the resulting data is stored on the server provided by OPEN. For security purposes, the data will be extracted from the OPEN server and transferred to a secure S4 server provided by SDU. All data management and handling will be carried out exclusively on the S4 server, adhering to the most stringent standards of data security and confidentiality.

### Statistical methods

To evaluate the effectiveness of the intervention, intention-to-treat analysis will be performed. The Generalized Estimating Equations model (GEE), which accounts for cluster randomization, will be utilized for data analysis. The model will be adjusted for the main potential confounding variables. Data analysis for this research will be conducted using RStudio (RStudio Team, 2022), a widely used open-source integrated development environment for the R programming language. Statistical significance set at *P* < 0.05. Ad-hoc analyses will also be conducted as necessary to support future hypotheses. Missing data, will adhere to the guidelines specific to each patient-reported outcome measure, ensuring appropriate and validated methods are utilized for each case. This approach ensures the integrity and validity of our data, even when some values are missing.

Descriptive statistics, we provide measures of central tendency (mean or median) and dispersion (standard deviation or interquartile range) for continuous variables, and frequencies and percentages for categorical variables. This comprehensive presentation of data will facilitate a clear and thorough understanding of the demographic and clinical characteristics of the study population.

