**Methods and intervention:**

The study is designed as a cluster-randomized trial with the intervention focusing on four key elements of diabetes care: effective cross-sectoral communication and information sharing, systematic care, a “one-stop-shop” health screening and start-up conversation at the municipality, and improving patient insights into own care.

This study requires 32 clusters (16/arm) to achieve 80% power and a 5% significance cut-off, with 270 patients required. GP recruitment occurred from May to Dec 2022. Patient recruitment is ongoing from May 2022 to Aug 2023. GPs were randomized 1:1 using computer-generated blocks of six.

Participating GPs are located in Southern Denmark and are not participating in other trials. Patients must be 18 + years of age, have a T2DM diagnosis, and be fluent in spoken and written Danish. DD is the primary outcome and will be measured at baseline, at four months, and again at a 12-month follow-up. Secondary outcomes include quality of care, self-management, quality of life, and clinical factors. Tertiary outcomes comprise depression, stress, resilience, sleep quality, and social network quality.

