### Sample size

The required minimum number of clusters (a cluster being one general practice, which can include several general practitioners) was calculated, based on the means and standard deviations (changes in DD from baseline to follow-up) reported in the REDEEM trial conducted by Fisher et al. [24]. Assuming a low intraclass correlation of 0.05 (https://www.ncbi.nlm.nih.gov/pmc/articles/PMC4983799/) and a mean group cluster size of 6 T2DM patients observed per year in the control and intervention groups, it was determined that 32 clusters (16 in each arm) are needed to achieve power at 80% and a statistical significance level of 5%. Although a dropout rate of 40% is considered high, it is likely for the present study due to the comprehensive patient-reported outcomes, which require three follow-ups. As such, a total of 270 patients are required for analysis.

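### The GEE is planned around a minimum of 32 practices with no small-sample correction or reference distribution stated; an uncorrected robust z test would run at roughly 7–8%, not 5%

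*Protocol article*

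**What the plan says.** The Statistical methods section of the protocol article names a single model: "The Generalized Estimating Equations model (GEE), which accounts for cluster randomization, will be utilized for data analysis". It adds "The model will be adjusted for the main potential confounding variables" without listing the covariates, and sets significance at P < 0.05. It does not say whether standard errors are model-based, robust or bias-corrected, whether the reference distribution is normal or t, or which working correlation applies.

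The abstract states "This study requires 32 clusters (16/arm) to achieve 80% power". The Sample size section presents this figure as the minimum number of clusters and defines the unit as "a cluster being one general practice, which can include several general practitioners". Its other inputs are "Assuming a low intraclass correlation of 0.05" and "a mean group cluster size of 6 T2DM patients observed per year in the control and intervention groups". The variation in cluster size is not given. Nor is the number of practices actually randomized, although GP recruitment had closed.

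**The concern.** Naming GEE settles that clustering is allowed for. It does not settle that the test holds its level. The customary robust (sandwich) variance with a normal reference is justified when clusters are many. With few clusters two things go wrong in the same direction: the sandwich variance is biased downward, and the normal critical value ignores the uncertainty in that variance. Unequal cluster sizes and covariates, especially cluster-level ones, add to the bias.

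Both aggravating features are plausible here. Practices were stratified as having 1–2 or 3 or more capacities, and the Study setting section expects 6–8 diagnoses per capacity per year, so recruitment per practice is likely to be unequal. Adjustment is planned. At stake is whether the confidence interval for the effect on diabetes distress has its nominal coverage and whether the stated 5% level is the real one.

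**Working it through.** **Inputs from the article.** 32 clusters, 1:1; ICC 0.05; mean cluster size 6; 5% level (taken as two-sided); 80% power; 40% dropout; 270 patients.

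**Assumptions, because the article is silent.** Coefficient of variation (CV) of cluster size 0 to 0.9; 0 to 3 practice-level and 0 to 4 patient-level covariates; Gaussian outcome; one follow-up score per patient; exchangeable working correlation. Mean size was varied from 3.6 (6 × 0.6) to 8.4 (270/32), and the ICC from 0.01 to 0.10.

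**The plan's own figure.** The 32 clusters cannot be reproduced, because no effect size or SD is printed. Working backwards: design effect 1 + (6 − 1) × 0.05 = 1.25; patients per arm 16 × 6 = 96; detectable standardized difference (1.960 + 0.842) × √(2 × 1.25/96) = 0.452. This value is used only to price the fix.

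**Analytic approximation, equal clusters, no covariates.**
- Normal critical value when the statistic follows t with 30 df: 2 × P(t₃₀ > 1.96) = 5.9%.
- Adding sandwich shrinkage of the standard error by √(30/32) = 0.968: 2 × P(t₃₀ > 1.96 × 0.968) = 6.7%.
- The same approximation with more practices: 6.4% at 40 and 5.9% at 60. The excess shrinks with cluster number.

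**Simulation under the null.** 32 clusters, 6,000 runs per row; Monte Carlo standard error about 0.3–0.4 points. KC is Kauermann-Carroll and MD is Mancl-DeRouen; the t reference has clusters − 2 − practice-level covariates as df. The last column is the mean uncorrected standard error divided by the true standard deviation of the estimate.

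| Mean size | Size CV | ICC | Covariates (practice + patient) | Uncorrected, z | KC, t | MD, t | SE ratio |
|---|---|---|---|---|---|---|---|
| 6 | 0 | 0.05 | 0 + 0 | 6.7% | 5.0% | 4.3% | 0.96 |
| 6 | 0.6 | 0.05 | 0 + 0 | 7.9% | 5.5% | 4.5% | 0.93 |
| 8.4 | 0.6 | 0.05 | 0 + 0 | 8.0% | 6.0% | 5.1% | 0.92 |
| 3.6 | 0.6 | 0.05 | 0 + 0 | 8.0% | 5.8% | 4.8% | 0.92 |
| 8.4 | 0.6 | 0.05 | 1 + 3 | 8.6% | 6.0% | 4.5% | 0.91 |
| 6 | 0.6 | 0.01 | 1 + 3 | 8.8% | 5.9% | 4.3% | 0.90 |
| 6 | 0.6 | 0.10 | 1 + 3 | 8.8% | 6.1% | 4.3% | 0.91 |
| 5 | 0.8 | 0.05 | 1 + 4 | 9.9% | 6.4% | 4.3% | 0.88 |
| 8.4 | 0.9 | 0.05 | 2 + 4 | 11.4% | 6.7% | 4.0% | 0.84 |
| 5 | 0.8 | 0.05 | 3 + 4 | 11.6% | 6.3% | 3.3% | 0.83 |

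The equal-size row agrees with the analytic 6.7%. ICC and mean size hardly matter; size variation and practice-level covariates do. Changing only the reference from z to t is not enough: the uncorrected variance with t still gives 5.8% in the first row and 10.2% in the last.

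**Price in power.** Non-centrality 0.452 × √(96/2.5) = 2.80. With the t₃₀ critical value of 2.042 in place of 1.960, power is 77.4% against 80%.

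**The case against.** The strongest objection is that the defect is read into silence. The article does not state an uncorrected sandwich variance or a normal reference, and a condensed protocol article commonly leaves such detail to a full protocol or SAP, neither of which is shown. A reader might infer that the trial will be analysed with no small-sample correction, that its interval is too narrow, and that its false-positive rate is 6–10%. The text does not support this: it neither specifies nor rules out a correction, and a bias-corrected GEE fits its wording equally well. This part of the objection stands, so the inflation must be stated conditionally.

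Two further parts stand. The 32 practices are a required minimum, not the number randomized. The upper figures rest on a size CV and a covariate count that the article does not give. It is also tempting to say that every added covariate makes matters worse. The runs add covariates in groups, so no effect per covariate is shown; at CV 0.6, four together moved the error only from about 8.0% to 8.6–8.8%.

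What does not stand is that nothing remains. The article chose the model and the level, presented GEE as accounting for the clustering, and planned a cluster number at which the customary form of that model misses the stated level even in the most favourable case examined. That makes it worth settling in writing.

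**Conclusion.** The point holds conditionally. If the customary uncorrected sandwich variance with a normal reference is used at 32 practices, the nominal 5% test has roughly 7–8% type I error under moderate assumptions (ICC 0.05, mean size about 6, size CV 0 to 0.6), and just under 9% with one practice-level and three patient-level covariates. It reaches about 10% or more only with strongly unequal practices (CV 0.8–0.9) and five or more covariates. The corresponding standard errors are about 4–10% too small in the moderate cases and up to 17% too small in the most extreme. These figures assume a Gaussian outcome, one follow-up score and exactly 32 practices.

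This is a cheap improvement to confirm or add, not an established error in the trial and not a condition for its validity.

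**What to change.** Before the primary analysis, and unless the SAP already does so, specify: GEE with practice as the cluster; a bias-corrected sandwich variance, Kauermann-Carroll or Mancl-DeRouen; and a t reference with degrees of freedom equal to the number of clusters minus the number of cluster-level parameters (30 for 32 practices with intercept and arm; 29 if the practice-size stratum is added).

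In the moderate scenarios this brings type I error to 5.0–6.1% (Kauermann-Carroll) or 4.3–5.1% (Mancl-DeRouen). In the harsher ones it gives 6.3–6.7% and 3.3–4.3% respectively, so Mancl-DeRouen is the safer choice if sizes prove very unequal or several practice-level covariates are kept, at the price of some conservatism. Choose one before the arms are compared, and state the number of practices randomized.

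The cost is one sentence and an option in the R code. With 30 df the critical value rises from 1.96 to 2.04, intervals widen slightly, and nominal power falls by about 3 points, from 80% to 77%.

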## Discussion

The primary aim of this study is to evaluate a cross-sectoral intervention targeting DD in newly diagnosed T2DM patients through increased cross-sectoral collaboration. The anticipated results of the study will comprise effective tools for improving overall collaboration between health care sectors. These tools are envisioned for direct incorporation into routine clinical practice and will thus contribute to improvements in the overall health and well-being of patients.

Despite every effort to minimize bias, this study has some limitations. The lack of blinding of GPs in the study not only introduces the possibility of differential intervention delivery but also raises concerns about selection bias in the inclusion of patients. General practitioners might inadvertently select patients with certain characteristics or conditions that could influence the study outcomes. Despite the potential for selection bias due to the lack of blinding of GPs, the study has communicated the importance of including all patients with clear and precise instructions. Emphasizing the significance of a diverse and representative patient population is crucial for the study’s success, as it helps to mitigate the risks associated with selection bias and ensures the findings are more generalizable. Another limitation is that the study includes only patients who are fluent in Danish and thus presumably disproportionately excludes people from immigrant and ethnic minority groups. However, research from the USA indicates that minoritized ethnic groups are often at increased risk of diabetes distress [25]. An English questionnaire translation was considered, but as ethnic minorities in Denmark primarily speak variations of either Hindi or Arabic, a multilingual translation was required to effectively deal with this limitation. This, however, was beyond our funding capacity and thus not possible Lastly, using PROs as the primary measure presents limitations, including subjectivity influenced by personal biases, emotions, and beliefs, which can result in inconsistent reporting. Recall bias may affect accuracy and reliability, as patients might struggle to remember details accurately, leading to underreporting or overreporting of symptoms. However, as DD only can be measured using PROs, they are essential and offer unique insights into patients’ lived experiences which cannot be measured from clinical outcomes.

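### The primary model chooses covariates as potential confounders and does not commit to baseline DDS or the practice-size stratum, which may cost precision

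*Protocol article*

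**What the plan says.** The Statistical methods section commits to intention to treat ("To evaluate the effectiveness of the intervention, intention-to-treat analysis will be performed") and to a clustered model: "The Generalized Estimating Equations model (GEE), which accounts for cluster randomization, will be utilized for data analysis". On covariates it says only: "The model will be adjusted for the main potential confounding variables". It names no variable and gives no further rule for choosing one.

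Two obvious candidates appear elsewhere in the article but are not tied to that model:

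- **Practice size.** Under Allocation: "The GPs were stratified into two groups, taking their capacities into account". The strata are 1 or 2 capacities against 3 or more, within "GPs were randomized into intervention or control clusters at a 1:1 allocation ratio using a computer-generated block size of six".
- **Baseline DDS.** Under Primary outcome: "This study primarily investigates longitudinal changes in DD at baseline, 4 months, and 12 months". The Sample size section also works from change scores ("changes in DD from baseline to follow-up) reported in the REDEEM trial").

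The Discussion acknowledges a route to baseline differences between the arms: "General practitioners might inadvertently select patients with certain characteristics or conditions that could influence the study outcomes".

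**The concern.** In a randomised trial, covariates should be the design factors and the strong prognostic variables, named in advance. Potential confounding is a criterion from observational work. A variable balanced by stratification is not a confounder in that sense. A baseline already absorbed into a change score may not be thought of as one either. The stated rule could therefore miss both of the variables that most deserve a place, and it leaves room to choose covariates after baseline differences have been seen.

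Three things are at stake. The first is precision: a change score, or an arm-by-visit model with baseline as a free response, uses the baseline less efficiently than adjustment for it. The second is regression to the mean: if one arm starts with higher DDS, part of its later fall is expected without any intervention effect, and an unadjusted change score counts it as effect. With 32 clusters, and unblinded GPs recruiting the patients, a baseline difference is plausible. The third is agreement between analysis and design, because randomisation was stratified and nothing says that the stratum enters the model.

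**Working it through.** **The plan's own figures.** Inputs from the Sample size section: 16 clusters per arm, mean cluster size 6, ICC 0.05, 80% power, 5% significance (taken as two-sided), 40% dropout, 270 patients.

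- 32 × 6 = 192, and 192 × 1.4 = 268.8, which matches 270.
- Design effect: 1 + (6 − 1) × 0.05 = 1.25. Effective size per arm: 96 / 1.25 = 76.8.
- The effect and SD are not printed, so the 80% cannot be verified. It corresponds to a standardised difference in change of (1.960 + 0.842) × √(2 / 76.8) = 0.452.

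I take the 80% as given and ask how adjustment would move it.

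**Baseline DDS.** Assumptions not in the document: equal SDs at baseline and follow-up, correlation r between them, and the same ICC for change and adjusted scores, so that the design effect cancels. In units of the DDS variance:

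- change score: 2(1 − r)
- adjusted for baseline: 1 − r²
- ratio: (1 − r²) / [2(1 − r)] = (1 + r) / 2

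Power after adjustment, by normal approximation, is Φ(2.802 / √ratio − 1.960).

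| r | ratio | 2.802 / √ratio | power |
|---|---|---|---|
| 0.3 | 0.65 | 3.475 | 93.5% |
| 0.4 | 0.70 | 3.348 | 91.8% |
| 0.5 | 0.75 | 3.235 | 89.9% |
| 0.6 | 0.80 | 3.132 | 87.9% |
| 0.7 | 0.85 | 3.039 | 86.0% |
| 0.8 | 0.90 | 2.953 | 84.0% |

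The variance ratio does not depend on how many patients are finally analysed, but the starting power does:

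- If 270 are enrolled and 40% drop out, 270 × 0.6 = 162 remain, or 162 / 32 = 5.06 per cluster. The design effect is 1.20, the noncentrality 2.62 and the power about 75%. Adjustment raises this to 88% to 83% for r = 0.4 to 0.6.
- If 270 are actually analysed, at 8.44 per cluster, the design effect is 1.37 and the starting power about 89%.

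**Practice-size stratum.** Suppose the stratum explains a share R² of the between-cluster variance (assumed). The variance of a cluster mean is 0.95 / 6 + 0.05 = 0.2083 without the stratum and 0.1583 + 0.05(1 − R²) with it. If the stratum is ignored, the true two-sided error is 2[1 − Φ(1.960 / √ratio)].

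| R² | variance ratio | true alpha if ignored | power if included |
|---|---|---|---|
| 0 | 1.000 | 0.050 | 80% |
| 0.10 | 0.976 | 0.047 | 81% |
| 0.25 | 0.940 | 0.043 | 82% |
| 0.50 | 0.880 | 0.037 | 85% |

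Omission errs on the safe side, and at an ICC of 0.05 the effect is small.

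**The case against.** The strongest reply is that this is one paragraph in a journal article, and that a covariate list commonly sits in an analysis plan that is not shown. That stands as far as the list goes: its absence is no defect. It does not cover the criterion, which the article does state and which points the wrong way.

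Second, a reader might infer that the model discards precision and does not analyse as randomised. The documents do not support that. Intention to treat and clustering are both stated, neither variable is excluded, and both could be counted among the potential confounders. The outcome is framed as change, so baseline DDS is used in some form. No section specifies an unadjusted change score or a free baseline, so the gains in the first table hold only against that comparator.

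Third, if GPs' selection makes the arms differ systematically, concern with confounding is not misplaced, and adjustment for baseline is no longer plainly superior. With non-random differences it and the change score answer different questions, and either can be biased. This also stands. The Discussion says only that such selection might occur, and that clear instructions to include all patients were given.

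Fourth, the Blinding section says that data analysts are blinded. That limits steering the covariate choice towards a result. It does not fix the choice, since baseline differences between coded groups can still be seen.

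**Conclusion.** The point holds in limited form. The article states a poor rule for choosing covariates and does not commit the primary GEE to baseline DDS or to the stratum used in randomisation. Most of the weight falls on baseline DDS and the open covariate set. Against an unadjusted change-score or free-baseline analysis, adjustment would cut variance by 10% to 35% and lift a planned 80% to about 84% to 93%. This rests on an assumed correlation of 0.3 to 0.8, equal SDs and a common ICC. The stratum matters little: if practice size explains up to half of the between-cluster variance, omitting it puts the true alpha between 0.037 and 0.050.

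This should be corrected, but it does not invalidate the planned analysis. Nor should adjustment be presented as a cure for recruitment bias, because it deals with measured baseline DDS and leaves selection on unmeasured factors untouched.

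**What to change.** Replace the covariate sentence with:

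> The primary GEE will model DDS at 4 and 12 months (baseline not in the response vector) with arm, visit, arm × visit, baseline DDS (continuous) and the randomisation stratum (1–2 vs 3 or more capacities). Any further covariates are fixed before unblinding, and none is chosen from observed baseline differences.

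The bracket about the response vector matters: without it, baseline DDS would be both outcome and predictor. Secondary outcomes should use the same structure, each with its own baseline value.

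The cost is one sentence. Baseline DDS and practice capacity are already collected under the plan, and no visit, sample size or procedure changes.
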